## Abstract

**Background:**

Multiple sclerosis is one of the most prevalent neurological diseases in young adults affecting over 2 million people worldwide. Alemtuzumab is a highly effective therapy in relapsing remitting MS. Alemtuzumab is a monoclonal CD52 antibody that proved its efficacy against an active comparator (interferon [IFN]-β1a) in a phase II trial and two phase III trials regarding clinical and MRI outcomes. Nevertheless, the exact mode of action is still unknown. Alemtuzumab is commonly associated with secondary autoimmune disorders significantly affecting the risk-benefit ratio. Therefore, new biomarkers predicting treatment response and adverse events are urgently needed. This study aims to further elucidate the mechanism of action of the neuroprotective potential of alemtuzumab in relapsing-remitting multiple sclerosis (RRMS).

**Methods/Design:**

This is a 3-year multicentre, explorative study including overall 150 patients comprising three different groups: (i) de novo patients prior and after alemtuzumab treatment initiation, (ii) patients under alemtuzumab treatment and (iii) patients requiring more than two alemtuzumab infusions. Peripheral blood and serum samples will be collected semi-annually for several in vitro/ex vivo assays to detect and characterize immune cells including their functional activity. Furthermore, data of MRI scans and disease-related impairment (using EDSS and MSFC), as well as the number and time of relapses, will be assessed. The clinical study is registered at clinicaltrials.gov (NCT04082260).

**Perspective:**

Our study will provide deep insights into the underlying immunological changes in a longitudinal analysis of alemtuzumab treated RRMS patients. By combining clinical, radiological and functional immune-phenotype data, we will be able to identify biomarkers and/or immune signatures predicting treatment response and adverse events. Thereby, the understanding of the mechanisms of action of alemtuzumab will improve its efficacy and safety for present and future patients.

## Background

Multiple sclerosis affects over 2 million people worldwide and most commonly young adults usually above the second and below the fourth decade of life [1]. Pathological hallmarks of MS are inflammation, demyelination, oligodendrocyte death, axonal damage and neurodegeneration [2]. Therefore, many therapies have been established to modify the adaptive immune system to prevent progression of the disease. In 1991 the first MS patient had been treated with alemtuzumab, a humanized, monoclonal antibody selectively targeting CD52 which is expressed by T- and B-lymphocytes, NK cells, dendritic cells, monocytes and macrophages [3]. Since 2013 alemtuzumab has been approved for the treatment of RRMS by the EMA (European Medicine Agency) under the name Lemtrada®.

The two phase 3 approval trials CARE-MS I (Comparison of Alemtuzumab and Rebif Efficacy in Multiple Sclerosis) and CARE-MS II compared alemtuzumab with IFN-β1a therapy and included treatment- naïve or pre-treated RRMS patients. The 5-year evaluation of efficacy and safety data indicated that the annualized clinical relapse activity was reduced, most patients showed no evidence of disease activity, and the extent of brain volume loss was slowed, even though 68.5% [CARE-I] and 59.8% (CARE-MS II) of patients did not receive an additional alemtuzumab course after their second annual cycle [4, 5].

Alemtuzumab leads to sustained quantitative and qualitative changes within the immune system and is therefore considered a short-pulse immune reconstitution therapy, where 12 mg/day is i.v. administered for 5 consecutive days and followed by a 3-day treatment 12 months later. This treatment results in an initial depletion of lymphocytes followed by a slow repopulation. It was observed that B cells and NK cells recur fast within a matter of 3 to 6 months, while peripheral T cells are mostly undetectable for 12 to 18 months [6].

The most common adverse effects of alemtuzumab are infusion-associated reactions and infections, which occur at the highest rate after the first treatment course. Most relevant are secondary autoimmune events, including thyroid disease, immune thrombocytopenia and nephropathy [7]. The experiences of these trials led to the implementation of an extensive safety measures allowing for early recognition and therapy of adverse events. However, recently in April 2019 the EMA (European Medicine Agency) has initiated a review of alemtuzumab therapy, since new side effects were reported including immune-mediated diseases (autoimmune hepatitis, hemophagocytic lymphohistiocytosis) and cardiovascular disorders (lung bleedings, heart attacks, strokes and cervicocephalic arterial dissections). While the review is ongoing alemtuzumab use was restricted to patients with active relapsing-remitting multiple sclerosis despite a full and adequate course of treatment with at least two other disease-modifying therapies or to patients where all other disease-modifying therapies are contraindicated [8].

Alemtuzumab has demonstrated to be a highly effective therapy with a safety profile requiring specific precautions defined by a risk management program for RRMS. However, the mechanisms of action remain largely unknown [9]. Combining clinical, radiological and immunological data the present multicentre, explorative phase IV study aims to elucidate further insights into the mechanisms of action of alemtuzumab treatment and to identify biomarkers for treatment efficacy and safety. This study is supported by the German Federal Ministry for Education and Research (BMBF) as a project within the German Competence Network Multiple Sclerosis (Kompetenznetzwerk Multiple Sklerose, KKNMS).

## Methods

### Aim of the trial

To elucidate the mechanism of action and neuroprotective potential of alemtuzumab we aim to combine clinical data (MRI, EDSS, MSFC) with in vitro (e.g. isolation/stimulation of immune cell subsets, cytokine production, effector functions) and ex vivo (ten-colour flow cytometry from peripheral blood of alemtuzumab treated patients) data.

### Study description and study design

This study is a multicentre explorative phase IV study to elucidate further insight into the mechanisms of action of alemtuzumab treatment in patients with RRMS. We aim to include around 300 alemtuzumab treated MS patients. The study will be continued for 3 years with regular blood sampling every 6 months. The study will be conducted in multiple KKNMS centers and is supported by the German Federal Ministry for Education and Research (BMBF). Recruitment started in January 2017. Each patient’s study participation will be 3 years. With study inclusion and every 6 months during this time, there will be blood sampling and clinical assessments (anamnestic data, EDSS, MSFC) at the study center. MRI scans are part of the routine diagnostic of MS patients. The data from these scans will be correlated with clinical and experimental parameters. Scheduling will be based on the date treatment is initiated. If a patient is eligible for study participation, the baseline assessments listed in Table 1 are performed before treatment with alemtuzumab is started. If a patient experiences a relapse after clinical baseline assessments (EDSS, MSFC) and prior to initiation of alemtuzumab, the respective examination must be repeated before treatment is started. During the study period the patient will be examined every 6 months following the regular study procedures (see Table 1). All collected samples and data will be organized by professional biobanking which results in a highly controlled and standardized collection, storage and analysis of the biological samples.

**Table 1 Tab1:** Regular Study Procedures

Baseline assessments Month 0	Month 6, 12, 18, 24, 30 and 36 after treatment initiation
• Demographic information (date of birth, gender)	
• Determination and documentation of eligibility by the Investigator or authorized representative (according to eligibility criteria)	
• Relevant medical history: e.g., lumbar puncture, MRI, medication history and current medications, medical conditions/surgical history, clinical episode history	
• Physical examination and documentation of vital signs	• Physical examination and documentation of vital signs
• Adverse events and concomitant medication	• Adverse events and concomitant medication
• MSFC	• MSFC
• EDSS	• EDSS
• Collection of peripheral blood and serum for several in vitro and ex vivo assessments (8 × 9 ml EDTA blood, 2 × 9 ml serum) as part of the routine blood assessments (including complete blood count, serum creatinine levels, tests of thyroid function)	• Collection of peripheral blood and serum for several in vitro and ex vivo assessments (8 × 9 ml EDTA blood, 2 × 9 ml serum) as part of the routine blood assessments (including complete blood count, serum creatinine levels, tests of thyroid function)

The clinical study is registered at clinicaltrials.gov (NCT04082260). It will be performed in accordance with the approval of the local ethics committee (Ethik-Kommission der Ärztekammer Westfalen-Lippe und der Westfälischen Wilhelms-Universität Münster, 2014–398-f-S), the requirements of the current German drug law (“Arzneimittelgesetz”), the current legal provisions regarding data protection, and the principals of Good Clinical Practice. All participants are obliged to hand in the signed informed consent form (ICF).

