#### Sample size

At least 50 patients per group will be included in this study. The groups comprise three different groups: (i) de novo patients (until 04/2019), (ii) patients under alemtuzumab treatment and (iii) patients requiring more than two alemtuzumab infusions.

The sample size is justified by:

Cohen’s d (Δ/σ = difference of means/standard deviation) is a measure of effect size for mean differences of two groups with similar sample size. Cohen’s d is used to estimate the relevance of significant mean differences. The expected effect size can be estimated on the basis of data from previous studies:
Alemtuzumab leads to a decrease of absolute CD8^+^ T cell numbers in peripheral blood from 0,34 × 10^9^ ± 0,05 cells/L to 0,175 × 10^9^ ± 0,06 cells/L 6 months after treatment [15]. Here, Cohen‘s d equals 0,831.Alemtuzumab increases the concentration of BDNF (brain-derived neurotrophic factor) produced by peripheral blood mononuclear cells under MBP (myelin basic protein) stimulation from 200 ± 82 pg/mL to 290 ± 73 pg/ml 6 months after treatment [15]. Here, Cohen’s d equals 0,502.

Clinical studies define effect sizes of Δ/σ = 0,2–0,3 as small, Δ/σ = 0,3–0,8 as medium and Δ/σ > 0,8 as large. Based on previous data we are expecting medium to large effect sizes with a Cohen’s d of > 0,5. With a type I error of α = 0,05 and a power of 0,95 the required sample size equals 42.

The precision of this estimation is considered to be sufficient to track the condition of the immune system over time to describe the mechanisms of action of alemtuzumab treatment.

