### Limitations of the study

The approach of a multicentre study results in a higher rate of patient enrolment and improves the generalizability of the study. Nevertheless, multicentre studies have several disadvantages regarding the difference in the severity of the disease and the heterogeneity in clinical practice among centers, which is a major confounding factor for the interpretation of the results [21]. Therefore, a rigorous study protocol for uniform data collection was created. However, patient recruitment takes place in highly specialized centers for multiple sclerosis (centers of the Kompetenznetz Multiple Sklerose KKNMS) which might bias the patient pool, because these patients might have a more complicated and severe disease history, which could limit our results at least in part.

Furthermore, the outcome of the study might be influenced by the potential loss of follow ups. Patients who discontinue study participation or the treatment with alemtuzumab prematurely will not be replaced. To avoid an effect on the results we calculated that a sample size with at least 50 patients per each group (de novo patients; patients under alemtuzumab treatment; patients requiring more than two alemtuzumab infusions) is necessary to compensate potential loss of follow up.

Although we aim to elucidate the mechanism of action of the potential immune-reconstitutive effects of alemtuzumab within this study, the results might be limited since the data will only be generated from blood samples. Since the pathologic process of MS takes place in the CNS, it is still unknown how representative the lymphocyte populations/parameters in the peripheral blood samples may be, since the transmigration via the blood-brain barrier is a tightly regulated process and might be affected in disease and under therapy [22]. Further studies will be needed to characterize the immunological change and explore new biomarkers in the brain itself using animal models or potentially CSF analysis. However, the requirement for lumbar puncture constitutes a major barrier for more general use, especially when repeated lumbar punctures are needed.

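### Total enrolment is 150 in the abstract but about 300 in the study design section, and nothing in the article reconciles the two

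*Protocol article*

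**What the plan says.** The article gives the study's size in four places.

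- Abstract, Methods/Design: an "explorative study including overall 150 patients comprising three different groups".
- Methods, Study description and study design: "We aim to include around 300 alemtuzumab treated MS patients".
- Methods, Sample size: "At least 50 patients per group will be included in this study". The same section names the groups: "The groups comprise three different groups: (i) de novo patients (until 04/2019), (ii) patients under alemtuzumab treatment", and, third, patients who need more than two infusions.
- Limitations of the study: "we calculated that a sample size with at least 50 patients per each group" is needed to allow for loss to follow-up, and "Patients who discontinue study participation or the treatment with alemtuzumab prematurely will not be replaced".

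The per-group figure sits alongside a power calculation. The Sample size section says "we are expecting medium to large effect sizes with a Cohen’s d of > 0,5" and continues: "With a type I error of α = 0,05 and a power of 0,95 the required sample size equals 42".

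**The concern.** Total enrolment is a basic design parameter, and here it has two values, one twice the other. Both stand in current text that describes the plan. Neither belongs to an amendment log.

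A reader of the abstract expects 150 patients, and a reader of the Methods expects about 300. When results appear, a final count of 160 could be reported as slightly above plan or as little more than half of it, depending on which sentence is cited.

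The split of any additional patients is open as well. The de novo group is limited to the period up to April 2019, and the primary cell-count endpoints are changes from baseline. Where a further 150 patients would go therefore affects what they could contribute, and the article does not say.

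**Working it through.** **Inputs.** Abstract total: 150. Design-section total: about 300. Number of groups: 3 (Sample size; Arms and interventions). Minimum per group: 50 (Sample size; Limitations). Required size from the power statement: 42 (Sample size). No dropout rate is stated.

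**1. Reproduce the plan's figure.** 3 groups × 50 = 150. This equals the abstract's total exactly.

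**2. Try to reach 300.** 300 / 150 = 2. With three groups, 300 needs 300 / 3 = 100 per group. With groups of 50, it needs 300 / 50 = 6 groups. The article states neither.

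**3. Test whether attrition links the two totals.** The step from 42 to 50 implies an allowance of 1 − 42/50 = 0.16, and 42 / (1 − 0.16) = 50. If 300 were enrolled and 150 were completers, attrition would be 1 − 150/300 = 50%. If the evaluable target were 3 × 42 = 126, it would be 1 − 126/300 = 58%. Neither is close to 16%. The Limitations section also presents 50 per group as already covering loss to follow-up.

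**4. Test whether screening links them.** The design section speaks of patients to be included, not screened. The article gives no screening or biobank count.

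**5. Check what does not depend on the total.** The power statement gives 42, raised to at least 50 per group. It reads the same whether the total is 150 or 300. I take 42 as stated; whether it is correct is a separate question.

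**6. Illustration only: what the difference could mean for precision.** Assume an equal split, which the article does not state, and no dropout. The 95% confidence interval half-width for a mean change, in SD units of the change, is t(0.975, n − 1) / √n.

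| Total | n per group | Half-width (SD) |
|---|---|---|
| 150 | 50 | 2.0096 / √50 = 0.284 |
| 300 | 100 | 1.9842 / √100 = 0.198 |

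The ratio is 0.284 / 0.198 ≈ 1.43. The factor of two applies to patient numbers, while precision would differ by about 1.4. If the additional patients did not join the de novo group, that group's half-width would not change.

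**The case against.** The strongest reply is that 50 per group is a floor. A study of 300 satisfies it, so the Sample size and Limitations sections do not conflict with the design section. On this reading 300 is the recruitment aim and 150 the minimum. That is correct as far as those two sections go. It means the article does not establish 150 as the right figure. It does not remove the conflict with the abstract, which gives 150 as an overall number and does not call it a minimum. The approximate wording in the design section cannot stretch from 300 to 150.

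A second reply is that the study is exploratory. The Statistical methods section sets no significance levels and treats p-values as hypothesis-generating, so no confirmatory conclusion turns on the total. That also stands, and it limits the consequence. It does not make two different totals acceptable.

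A reader might go further and infer any of the following, none of which the article supports:

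- That the planned precision or a completion criterion is contradictory. The article gives no numeric precision target, only a judgement that precision is sufficient, and it states no completion criterion.
- That it is unclear which sample size the power statement describes. It describes 42.
- That the additional patients could only enter the already-treated groups. The April 2019 limit restricts when de novo patients could join, not how many. Recruitment had been open since January 2017.

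**Conclusion.** The point holds as an internal inconsistency. Total enrolment is stated as 150 in one place and about 300 in another, a twofold difference in patient number that the article does not explain. The only figure with a derivation is the minimum of 3 × 50 = 150. That favours 150 without proving that it is the intended total.

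This conclusion rests on the two sentences and one multiplication and needs no assumption about the analysis. The half-widths of 0.28 and 0.20 SD are illustrative and depend on an equal split across three groups.

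**What to change.** The sponsor should confirm one total and state it in both the abstract and the study design section.

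- If there is no stated basis for 300, align the design section to 150, with at least 50 per group.
- If 300 is the real recruitment aim, correct the abstract, give the planned number in each of the three groups in a way that respects the April 2019 limit on de novo patients, and present 150 as the minimum.
- If 300 is a biobank or screening figure, label it so and keep it out of the analysis size.

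The first and third options cost one sentence. The second costs a corrected abstract and one sentence on the split by group. The stated power calculation need not change for any of them.

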### Arms and interventions

The patient population will be patients with active RRMS. Different patient groups will be included: (i) de novo patients (until 04/2019) (ii) patients under alemtuzumab treatment (iii) patients requiring more than two alemtuzumab infusions.

### Outcome measures

#### Primary endpoints

Absolute and relative change of cell-counts compared to baseline of T cell subsets (CD4 and CD8 positive T cells: naïve T cells, T effector cells, T memory cells, regulatory T cells; T-helper subsets: Th1, Th2, Th17), B-cell subsets (recent bone marrow emigrants, mature naive, memory B cells and plasma cells), natural killer cells (CD56^bright^, CD56^dim^), natural killer T cells, antigen-presenting cells (Dendritic cells: CD303^+^ plasmacytoid, CD11c^+^ and CD141^+^ myeloid dendritic cells, monocytes and macrophages) and myeloid-derived suppressor cells in the peripheral blood samples at indicated time points of sampling will be considered as primary endpoints. Furthermore, markers of autoimmunity in the serum (ANA, cANCA, pANCA, anti-dsDNA, anti-TSHR, anti-TPO, RF, anti-CCP, anti-GBM and anti-platelet antibodies) will be considered as further primary endpoints (see Table 2).

**Table 2 Tab2:** Endpoints of the study

Primary Endpoints	
• T cell subsets: - CD4 and CD8 positive T cells: naïve T cells, T effector cells, T memory cells, regulatory T cells - T-helper subsets: Th1, Th2, Th17	
• B cell subsets: - Recent bone marrow emigrants, mature naïve, memory B cells - Plasma cells	
• Natural killer cells: - CD56bright, CD56dim - Natural killer T cells	
• Antigen-presenting cells: - Dendritic cells: CD303^+^ plasmacytoid, CD11c^+^ and CD141^+^ myeloid dendritic cells - Monocytes and macrophages	
• Myeloid-derived suppressor cells	
• Markers of autoimmunity in the serum (every 6 months): - ANA, cANCA, pANCA, anti-dsDNA, anti-TSHR, anti-TPO, RF, anti-CCP, anti-GBM, anti-platelet antibodies	
Secondary Endpoints	
• Activation status of cell surface receptors assessed by flow cytometry: - Relative and absolute change from baseline of mean fluorescence intensity (MFI) and the proportion of positive cells regarding CD25, HLA-DR, LFA-1, CD29, CD69, CD71 expression	
• Expression of co-inhibitory molecules assessed by flow cytometry: - Relative and absolute change from baseline of MFI and of the proportion of positive cells regarding PD-1 = CD279, ICOS = CD278, TIM-3, CTLA4 expression	
• Effector functions of CD4 and CD8 positive T cells: - Relative and absolute change from baseline of the results of cell proliferation assays assessed as the percentage of proliferated cells - Relative and absolute change from baseline of cytokine production measurement assessed as concentration - Relative and absolute change from baseline of the cytolytic activity assessed by flow cytometry measurement of MFI and proportion of positive cells regarding Granzyme B, Perforin and CD107a expression - Relative and absolute change from baseline of intracellular calcium response assessed as a ratio	
• Migrational capacity: - Relative and absolute change from baseline MFI and the proportion of positive cells assessed by flow cytometry expression analysis of CD11a, CD31, CD44, CD49d, CCR5, CCR6, CCR7 - Absolute and relative change of cell numbers of migrated cells compared to baseline assessed in an in vitro model by flow cytometry analysis	
• High-throughput TCR- and BCR sequencing of the T- and B cell rep-ertoire concerning the expansion of distinct clones: - Qualitative comparison of the distribution of CDR3 sequences	
• Regulatory T-cell function: - Relative and absolute change from baseline in production of TGF-beta and IL-10 of CD4^+^CD25^+^FOXP3^+^ regulatory T cells - Suppression of T cell proliferation: Relative and absolute change from baseline in responder T cell proliferation assessed by suppression assays	

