#### Statistical methods

Statistical analyses will be performed using standard statistical software like SAS or SPSS. The goal of this study is to detect the patterns in different populations of immune cells after treatment with alemtuzumab. Therefore, the analysis of the primary endpoints will focus on estimating the absolute and relative number of cells defined as primary endpoints summary statistics such as mean and standard deviation, median and quartiles, or frequency and percent, as appropriate. The development over time will be displayed using boxplots. To assess the difference of absolute or relative number of cells between two different time points statistical tests appropriate to the statistical distribution of the particular endpoint will be used (Wilcoxon signed-rank test, Student’s t-test for paired samples, Sign-Test). In order to compare more than two successive measurements, the preferred methods of statistical analysis are Repeated Measures ANOVA, Mixed Models and Generalized Estimation Equations, appropriately accounting for intra-individual correlations. Since this study is planned as an exploratory study, inferential statistics are intended to be exploratory (hypotheses generating), not confirmatory, and are interpreted accordingly. I.e., *p*-values are interpreted as a metric weight of evidence against the respective null hypothesis of no effect. Neither a global significance level nor local levels are determined. *P*-values are considered noticeable in case p < =0.05 and highly noticeable in case p < =0.01. These findings will be used to generate new hypotheses. Statistical analyses of the pre-specified secondary endpoints will be performed with appropriate descriptive and inductive statistical methods using summary statistics such as mean and standard deviation, median and quartiles, or frequency and percent. Appropriate to the characteristics of the endpoints, statistical tests like Fisher’s exact test, Chi-Square test, Mann-Whitney-U test, Wilcoxon signed-rank test or Student’s t-test will be performed.

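### In the de novo group, change from baseline may partly reflect the wearing off of an earlier MS drug, because neither the baseline definition nor the named paired tests account for prior therapy

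*Protocol article*

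**What the plan says.** The primary cell endpoints are "Absolute and relative change of cell-counts compared to baseline of T cell subsets", with the same measure for B cells, natural killer cells, antigen-presenting cells and myeloid-derived suppressor cells (Primary endpoints). On timing, Study description and study design says only that "the baseline assessments listed in Table 1 are performed before treatment with alemtuzumab is started".

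The abstract describes the first group as "i) de novo patients prior and after alemtuzumab treatment initiation", and Arms and interventions lists "i) de novo patients (until 04/2019) (ii) patients under alemtuzumab treatment" and patients requiring more than two infusions. De novo therefore means new to alemtuzumab. Nowhere is it defined as new to all MS drugs. It is also the only group described as having a sample from before alemtuzumab.

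Eligibility criteria makes Table 3 the governing list. Its three inclusion and seven exclusion criteria do not mention earlier or current disease-modifying drugs, or time since the last one. The same section says that patients receive alemtuzumab whether or not they join the study.

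Table 1 records "medication history and current medications" at baseline. Statistical methods gives this information no role. "To assess the difference of absolute or relative number of cells between two different time points", it names the Wilcoxon signed-rank, paired t and sign tests. For more than two measurements it prefers repeated-measures ANOVA, mixed models and generalized estimating equations (GEE), and mentions only the correlation within patients. Limitations of the study covers disease severity, centre practice, loss to follow-up and blood-only sampling, but not prior therapy.

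**The concern.** The study has no untreated comparator, so the Month 0 sample is the whole reference for a change from baseline and the denominator of every relative change. The Background section itself says that "many therapies have been established to modify the adaptive immune system to prevent progression of the disease". That is the compartment these endpoints count.

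Two patients who reach the same cell level after alemtuzumab will show different changes if one starts untreated and the other starts while an earlier drug is still lowering or raising the same subset. The contrast from Month 0 to a later visit then contains the effect of alemtuzumab plus the offset of the earlier drug.

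The study aims to find immune signatures that predict response and secondary autoimmunity. If baselines differ by last drug, a signature built on change scores may partly mark prior therapy. Most secondary endpoints are also changes from baseline and share the weakness. The article guards the clinical baseline, since EDSS and MSFC are repeated after a relapse that precedes treatment, but it describes no similar care for the immune baseline.

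**Working it through.** The point rests on the passages above and not on a stated figure. The arithmetic only shows what plausible carry-over could do.

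**Inputs from the article (Sample size):** mean CD8 count 0.34 × 10^9/L before treatment and 0.175 × 10^9/L at 6 months.

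**Change implied by those means:** 0.175 − 0.34 = −0.165 × 10^9/L; relative change −0.165 / 0.34 = −48.5%.

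**Assumptions that are not in the article:**
- These means are free of carry-over.
- A share q of patients, 25-75%, has a baseline shifted by a fraction c, 10-30%, through the previous drug.
- The Month 6 level is not affected by the previous drug.

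**Formulas:**
- Observed baseline mean = 0.34 × (1 ± q·c)
- Observed change = 0.175 − observed baseline mean
- Share of true change = observed change / (−0.165)
- Relative change of the means = observed change / observed baseline mean

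| q | c | Direction | Baseline | Change | Share of true change | Relative change |
|---|---|---|---|---|---|---|
| 25% | 10% | lowered | 0.3315 | −0.1565 | 95% | −47.2% |
| 50% | 20% | lowered | 0.3060 | −0.1310 | 79% | −42.8% |
| 75% | 30% | lowered | 0.2635 | −0.0885 | 54% | −33.6% |
| 25% | 10% | raised | 0.3485 | −0.1735 | 105% | −49.8% |
| 50% | 20% | raised | 0.3740 | −0.1990 | 121% | −53.2% |
| 75% | 30% | raised | 0.4165 | −0.2415 | 146% | −58.0% |

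For the third row: 0.34 × (1 − 0.75 × 0.30) = 0.2635; 0.175 − 0.2635 = −0.0885; 0.0885 / 0.165 = 0.536.

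The shift in the mean change is 0.34·q·c in size. It does not depend on the number of patients, so it is a bias that a larger sample would not reduce.

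**Can the named methods remove it?** The three two-time-point tests use only the within-patient differences and have no place for a covariate. Mixed models and GEE can carry one. A main effect of prior drug would move all visits by the same amount and leave the estimated change untouched, so the term has to interact with visit.

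**The case against.** The strongest reply is that covariates, strata and sensitivity subsets normally belong in a statistical analysis plan, which is not at hand, and that change from baseline is an ordinary endpoint. This stands in part. Mixed models and GEE are already named and could carry prior therapy, so it would be wrong to say that the article rules out adjustment. But the endpoint, the governing eligibility table and the paired tests are stated in the article, and together they leave the problem open.

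A second reply is that treatment is routine care, so the study cannot dictate an interval after an earlier drug. That is accepted, and it is why the remedy lies in the analysis.

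Third, the study is declared exploratory, and its biomarkers are said to need validation. This lowers the stakes but does not make a shifted reference sound for generating hypotheses.

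A reader might also draw four stronger conclusions that the article does not support:
- **That de novo patients were mostly pre-treated.** The Background section reports a restriction to patients with active disease despite "at least two other disease-modifying therapies or to patients where all other disease-modifying therapies are contraindicated". It dates from April 2019, and de novo entry ran only until 04/2019, so it says nothing firm about this group.
- **That carry-over could make the depletion vanish.** With a Month 6 level of 0.175, a baseline halved to 0.170 gives +2.9%. For a group mean, that requires an assumed halving in every patient.
- **That the data for adjustment are certainly in hand.** Table 1 mentions medication history but does not state last-dose dates.
- **That absolute levels are left out.** Statistical methods already summarises absolute cell numbers and shows them over time in boxplots. Comparisons between two visits after treatment do not use the Month 0 value at all.

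**Conclusion.** The concern holds in a limited form. In the de novo group, change from baseline may partly reflect offset of the previous drug, because the reference sample is defined only by the start of alemtuzumab and the paired tests cannot separate the two.

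The direction and size are unknown. The article does not give the pre-treated share, the drugs used or the time since last dose. The range of 54-95% (baselines lowered) or 105-146% (raised) of the true Month 6 CD8 change depends entirely on the assumed shares and shifts. Even at the far end of the lowered range, a clear fall in CD8 cells remains. The calculation shows a shifted reference only. It does not show that waning of an earlier drug would be mistaken for repopulation at later visits. Patients entering already on alemtuzumab are outside this point.

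**What to change.** No change to eligibility or clinical switching is needed.

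- **Statistical methods:** present the de novo change-from-baseline results by prior-therapy status, with treatment-naive or not recently treated patients in one stratum and recently or currently treated patients in the other. Fix the cut-off before analysis. In the mixed models or GEE already named, include last drug class and time since last dose, each interacting with visit.
- **Table 1:** confirm that medication history captures the stop date of the last disease-modifying drug. If it does not, retrieve the date from the clinical record where possible.
- **Limitations of the study:** add prior therapy.

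The cost is mainly analysis wording, plus any retrieval of missing stop dates. The drawback is smaller strata and wider intervals in a group of about 50, so the stratified results should be read as descriptive.
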